**Methods:**

In this Randomized Control Trial (RCT), 60 subjects with chemotherapy-induced cognitive impairments secondary to any cancer will be randomised into 2 groups by the sequentially numbered opaque sealed envelope approach. The cognitive functions will be measured as the outcome measures, which include all the recall strategies, executive function tasks, information processing speed, and attention.
Both groups will receive intervention every day for 4 weeks. Wilcoxon signed the rank test for data analysis, and students paired the “t” test, which will be used to study within-group effects. Mann-Whitney U Test and students Unpaired “t” Test will be used to compare groups at pre-treatment and post-treatment.

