## Methods

### Trial Design

This is an equal allocation, parallel-group, 2-arm superiority study, with the sample size distributed equally between the 2 groups. Patients will be evaluated according to predetermined inclusion and exclusion criteria and will be recruited from Siddharth Gupta Memorial Cancer Hospital in Sawangi, which is affiliated with Acharya Vinoba Bhave Rural Hospital. After obtaining informed consent, eligible participants will be selected through simple random sampling using computer-generated random numbers. All patients will be informed about the study procedures and asked to provide written consent before participation. The trial will include patients with a medical diagnosis of cancer who are currently undergoing chemotherapy. Sequence generation will be performed using computer-generated random numbers.

The allocation concealment mechanism will involve simple random sampling. Study participants will be randomly assigned using computer-generated random numbers. Randomization will be conducted by a researcher not involved in participant recruitment. To ensure allocation concealment, opaque sealed envelopes will be used, which will be opened only after participants are deemed eligible for treatment by the research team. Data collection will be carried out after participants are assigned to their respective intervention groups, with outcomes assessed and recorded during the preintervention phase. Postintervention data collection will be conducted after 4 weeks of intervention.

In data management, information obtained will be summarized using frequency and percentage for qualitative data, and mean and SD for quantitative data. Figure 1 presents the CONSORT (Consolidated Standards of Reporting Trials) flow diagram outlining the study design. See Multimedia Appendix 1 for the SPIRIT (Standard Protocol Items: Recommendations for Interventional Trials) checklist.

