### Selection of Participants

After obtaining ethical clearance from the Institutional Ethics Committee, patients diagnosed with cancer and scheduled to undergo chemotherapy will be identified at Siddharth Gupta Memorial Cancer Hospital. Permission will be sought from the treating residents, and eligible patients who meet the inclusion criteria will be enrolled after obtaining informed consent. Treatment will commence within 1 week of initiating the chemotherapeutic agent, and baseline data will be recorded. Participants will receive cognitive rehabilitation focusing on memory, attention, information processing, and executive function, with the aim of enhancing cognitive performance and improving quality of life. The first outcome measure, the Mini-Mental State Examination (MMSE), will be administered before the initiation of chemotherapy along with baseline data to assess cognitive function. Subsequently, the Montreal Cognitive Assessment will be conducted over 4 chemotherapy cycles. Participants will undergo the intervention 5 days per week, and following the completion of the 4 chemotherapy cycles, postintervention baseline data will be recorded. The outcome measures will be used to assess the degree of cognitive impairment. Follow-up assessments will be conducted after each chemotherapy cycle and weekly after completion of the intervention. Baseline outcome measures will be recorded after 4 chemotherapy cycles, and follow-up evaluations will be carried out once a week for 4 consecutive weeks.

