### Participant Timeline

Pre- and postbaseline data will be collected, followed by a 4-week intervention period. After the completion of the 4 weeks, postintervention outcomes will be assessed. The study design is illustrated in the CONSORT flowchart presented in Figure 1.

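### The post-intervention assessment is set both after 4 weeks of intervention and after 4 chemotherapy cycles, and no primary visit is named

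*Protocol article*

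**What the plan says.** Two sections tie the post-intervention assessment to the length of the programme. Trial Design: "Postintervention data collection will be conducted after 4 weeks of intervention". Participant Timeline: "After the completion of the 4 weeks, postintervention outcomes will be assessed". The programme length agrees with this elsewhere. The abstract has "Both groups will receive intervention every day for 4 weeks", and Control Group also gives 4 weeks.

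Selection of Participants ties it to chemotherapy instead: "following the completion of the 4 chemotherapy cycles, postintervention baseline data will be recorded". It repeats the timing and uses the word baseline again: "Baseline outcome measures will be recorded after 4 chemotherapy cycles, and follow-up evaluations will be carried out once a week for 4 consecutive weeks". The same section adds further occasions, "Follow-up assessments will be conducted after each chemotherapy cycle and weekly after completion of the intervention", and spreads one primary outcome over the whole period: "Subsequently, the Montreal Cognitive Assessment will be conducted over 4 chemotherapy cycles". The start is fixed by "Treatment will commence within 1 week of initiating the chemotherapeutic agent, and baseline data will be recorded".

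Outcome Measures lists three primary instruments (MMSE, Montreal Cognitive Assessment, FACT-Cognitive) and gives no time for any of them. The abstract compares groups before and after treatment. Statistical Analysis plans effect sizes for the MMSE and the Montreal Cognitive Assessment at several visits and names none as primary. Inclusion Criteria asks for at least 4 planned cycles. No section gives a cycle length.

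**The concern.** Both timings are called postintervention, so the visit after cycle 4 cannot be read simply as a later follow-up added to a 4-week endpoint. Staff scheduling visits could follow either section and be in line with the document.

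The choice changes what the trial estimates. If training stops at 4 weeks, the 4-week visit measures its immediate effect while the four cycles are still incomplete, and the visit after cycle 4 measures what is left after a gap without training. If training runs through the four cycles, the visit after cycle 4 is the end of treatment and the 4-week visit falls partway through it.

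Using the word baseline for data recorded after the intervention also blurs which record is the pre-treatment value in the within-group comparison. And while the main between-group comparison has no single time attached, the visit could in principle be settled after the results are known.

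**Working it through.** **The plan's own figure.** The Sample Size section gives 2 × (1.96 + 0.84)² / 0.8² + 1.96² / 4 = 24.5 + 0.96 = 25.46, rounded up to 26 per group, and adds 4 for dropout to reach 30. The 26 reproduces. It does not depend on the visit, because the effect size of 0.8 is not tied to any outcome or time. The point here therefore leaves the sample size alone.

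**The timings side by side.**

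| Section | Post-intervention assessment | Programme length |
|---|---|---|
| Abstract, Methods | after treatment, no time given | 4 weeks |
| Trial Design | after 4 weeks | 4 weeks |
| Participant Timeline | after 4 weeks | 4 weeks |
| Control Group | not given | 4 weeks |
| Selection of Participants | after 4 cycles, called baseline | 5 days a week, end not stated |

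**Can the two times coincide?** Let *c* be the cycle length in weeks (an assumption, since the document gives none). Four cycles last 4*c* weeks. A programme that starts with chemotherapy ends at week 4, so the gap is 4*c* − 4.

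- *c* = 1: 4 − 4 = 0 weeks
- *c* = 2: 8 − 4 = 4 weeks
- *c* = 3: 12 − 4 = 8 weeks
- *c* = 4: 16 − 4 = 12 weeks

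A start up to 1 week after chemotherapy begins, which the text allows, shortens each positive gap by at most 1 week. The times then meet at *c* = 5/4 = 1.25 weeks. So they coincide only with cycles of about 1 week. At week 4 of chemotherapy, 4/*c* = 2, 1.3 or 1 cycles are complete for *c* = 2, 3 or 4.

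**What an open choice between the two times could do to the error rate.** Take one outcome with no true effect, tested at two-sided 5% at each time, with the more favourable result reported. With independent visits the error is 1 − 0.95² = 0.0975. Repeated measures on the same patients are correlated, so two-sample *t* tests were simulated with 26 per group and 20,000 replicates:

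| Assumed between-visit correlation | Type I error |
|---|---|
| 0.5 | 0.092 |
| 0.7 | 0.086 |
| 0.9 | 0.069 |

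The document gives no correlation, so the range of 7% to 9% rests on these assumed values.

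**The case against.** Four sections agree on 4 weeks, either for the assessment or for the programme, and the outlier is a section on recruiting participants. A reader could take 4 weeks as the intended time. The statistical analysis plan may name a primary visit, and the flow diagram that Participant Timeline cites is not shown. This has weight: it makes the problem a contradiction to reconcile rather than an endpoint with no definition at all. It does not remove the problem, because a condensed article may leave out detail but should not give two incompatible times for one assessment. A visit named elsewhere would still leave these sections in conflict.

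Several stronger readings are tempting, and the document does not support them.

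- **The visit will be picked from the results.** No section says so. Statistical Analysis points to reporting effect sizes at several visits.
- **The family-wise error is 21% to 24%.** Three outcomes at two visits do give 24.4% (correlation 0.5 within and 0.15 across outcomes) and 21.3% (0.7 and 0.35). But three outcomes at one fixed visit already give 14.1% and 13.4% with the same cross-outcome values. Most of the figure therefore comes from having three primary outcomes, which is a separate matter. The open visit adds about 10 and 8 percentage points.
- **The later visit measures retention after all chemotherapy.** Inclusion Criteria sets 4 cycles as a minimum, so chemotherapy may continue beyond cycle 4. The word retention also presumes that training stops at 4 weeks, which is part of what is unsettled.
- **The comparison is biased by unequal intervals.** If visits follow cycle length, intervals may differ between patients, but this arises in both randomised arms. It mainly adds variance and blurs the question being answered. No bias between arms has been shown.

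**Conclusion.** The contradiction stands in the current text and should be resolved before any between-arm comparison. The post-intervention assessment has two times that agree only if cycles last about 1 week, the later one is labelled baseline, and no section makes either one primary. Under assumed cycles of 2 to 4 weeks the times are 4 to 12 weeks apart (up to 1 week less with a later start), enough for them to answer different questions. The effect on the error rate is moderate: about 7% to 9% for one outcome instead of 5%, under assumed correlations of 0.9 to 0.5, and only if the better of the two times were in fact reported. The larger consequence is that the main comparison cannot be carried out as written without someone deciding which section to follow.

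**What to change.** The order matters.

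1. Reconcile the intervention length and the time of the post-intervention assessment across the abstract, Trial Design, Selection of Participants, Participant Timeline and Control Group. Which schedule applies is for the investigators to state. Naming the visit before this is settled could place the primary assessment partway through the intervention.
2. Then, before outcomes are compared between arms, name one primary analysis visit for the primary outcomes, with a window and the same timing in both arms. Include the Montreal Cognitive Assessment, which at present is spread over the cycles.
3. Label every other assessment, whether after a cycle or weekly, as secondary.
4. Use the word baseline only for data recorded before the intervention starts.

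The cost is a dated wording amendment, and the sample size does not change. One caution applies: Selection of Participants lists no separate 4-week visit, so the investigators should check that the visit they name is actually being held for every participant.

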### Control Group

Participants will perform aerobic exercises and cognitive behavioral training daily. The program will include brisk walking, cycling, jogging, and cognitive skill activities for 45 minutes per day, 5 days a week, over 4 weeks. These activities will not require direct supervision.

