### Statistical Analysis

For demographic factors, all data will be summarized using baseline characteristics, expressed as the mean and SD for continuous data and as frequency and percentage for categorical data.

The analysis of outcome variables will primarily focus on continuous variables. For parametric data, the minimum, maximum, mean, SD, SE, and 95% CI will be summarized. The normality of continuous outcome variables will first be tested using the Kolmogorov-Smirnov test at a 5% level of significance (*P*≤.05). If the data are found to deviate from normality, a nonparametric test will be applied to determine significance. An independent *t* test will be conducted for group comparisons to assess significant differences at the 5% level (*P*≤.05). The intervention groups will receive (1) cognitive training supplementing traditional physical treatment and (2) traditional physical treatment.

The effect size at different assessment visits between the 2 groups will be calculated for the variables MMSE and Montreal Cognitive Assessment. For nonnormal data, descriptive statistics will include the mean, median, and lower and upper quartiles. The Mann-Whitney test will be applied to determine statistical significance when nonparametric methods are required.

Categorical variables will be summarized using frequency (n) and percentage. Chi-square analysis will be performed to evaluate efficacy across categorical variables. An intention-to-treat analysis will be applied to minimize attrition bias among participants, including those lost to follow-up or deceased due to adverse effects of chemotherapeutic drugs.

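### Paired within-arm tests on the cognitive screens cannot show that a programme works, because retest gain alone can make them significant; efficacy should rest on the between-arm comparison

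*Protocol article*

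**What the plan says.** **Within-arm tests.** The Methods paragraph of the abstract names the Wilcoxon signed-rank test and the paired t test, "which will be used to study within-group effects". It gives the unpaired t and Mann-Whitney tests for comparing the groups before and after treatment. The Statistical Analysis section describes only the between-group tests and adds: "The effect size at different assessment visits between the 2 groups will be calculated for the variables MMSE and Montreal Cognitive Assessment".

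**Objectives.** There are three: the effect of cognitive rehabilitation on cognition, its effectiveness against conventional therapy, and its effect on quality of life. Only the second is worded as a comparison.

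**Assessment times.** Selection of Participants says the MMSE "will be administered before the initiation of chemotherapy along with baseline data to assess cognitive function". It continues: "Subsequently, the Montreal Cognitive Assessment will be conducted over 4 chemotherapy cycles". It then says "Follow-up assessments will be conducted after each chemotherapy cycle and weekly after completion of the intervention", and that after 4 cycles "follow-up evaluations will be carried out once a week for 4 consecutive weeks". It does not name the instruments used at these follow-up visits. Trial Design has a pre-intervention assessment and then: "Postintervention data collection will be conducted after 4 weeks of intervention". Participant Timeline agrees with Trial Design.

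**The concern.** The MMSE and the Montreal Cognitive Assessment are short performance tests that include memory items, so scores can rise with familiarity. A paired test cannot separate that rise from benefit, because no untreated or comparison data enter it. Randomisation protects the contrast between arms, not the change inside one arm.

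This matters because of how the objectives are worded. The first and third ask about the effect of rehabilitation without naming a comparator, so a significant pre-to-post change in the rehabilitation arm is the natural result to quote for them. The trial could then report improved cognition although neither programme did anything, and although the between-arm test showed no difference. More repeat testing before the post-intervention visit would probably enlarge the gain, and the article does not settle how many such tests there are.

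**Working it through.** **1. The plan's own sample size.** Inputs from Sample Size: d = 0.8, Z = 1.96 and 0.84, ratio 1.

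2 × (1.96 + 0.84)² / 0.8² + 1.96² / 4 = 24.5 + 0.96 = 25.46, rounded up to 26 per group; with the dropout allowance, 30. The stated figures reproduce. They do not depend on the number of assessments. Both 26 and 30 are used below.

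**2. How many assessments?**
- Selection of Participants, on its fullest reading: 1 baseline + 4 after cycles + 4 weekly = 9.
- Trial Design and Participant Timeline: 1 before + 1 after = 2.
- By name, the MMSE is dated once and the Montreal Cognitive Assessment is placed over the 4 cycles.

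So 9 per instrument is an upper reading, not a stated count. The weekly visits follow the intervention. If the post-intervention measurement comes first, those visits cannot affect the pre-to-post change.

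**3. Paired test with no treatment effect.** Let g be the mean retest gain divided by the SD of change. The paired t statistic follows a noncentral t distribution with n − 1 degrees of freedom and noncentrality g√n. The test is two-sided at 5%. The critical value is 2.060 for n = 26 and 2.045 for n = 30. The values of g are assumptions.

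| g | g√26 | significant, n = 26 | g√30 | significant, n = 30 |
|---|---|---|---|---|
| 0 | 0 | 5% | 0 | 5% |
| 0.3 | 1.53 | 31% | 1.64 | 36% |
| 0.4 | 2.04 | 50% | 2.19 | 56% |
| 0.5 | 2.55 | 69% | 2.74 | 75% |

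**4. Both tests side by side.** This is a simulation with 26 per arm, no treatment effect, the same gain in both arms, an assumed pre-post correlation of 0.7 and 20,000 runs. Here the gain is in SD of the score, not SD of change.

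| Common gain | Paired test within one arm | Unpaired test between arms |
|---|---|---|
| 0 | 5.2% | 5.1% |
| 0.2 | 24.7% | 5.1% |
| 0.4 | 71.4% | 5.0% |
| 0.6 | 96.5% | 4.8% |

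The two scales agree. The SD of change is √(2 × (1 − 0.7)) = 0.775 SD of the score, so a gain of 0.4 SD is g = 0.4 / 0.775 = 0.52, just above the last row of the first table.

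**5. If exposure did differ by arm.** Assume a total gain of 0.4 SD that builds up linearly over 8 retests, with one arm attending all 8. If the other attends 7, 6 or 4, the bias is 0.4 × 1/8, 2/8 or 4/8 = 0.05, 0.10 or 0.20 SD. The between-arm test then rejects in about 5.5%, 6.2% or 11% of trials.

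**The case against.** The trial is a randomised superiority study with equal allocation, and the arms are compared by unpaired tests. No section gives the arms different assessment times, so a shared retest gain cancels. The paired tests appear only in the abstract. This stands for the superiority comparison, and the second table in the working bears it out. It does not rescue the paired tests, which remain planned, nor the two objectives that name no comparator.

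The objection also disposes of three stronger readings that a reader might infer.

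- *Retest learning contaminates the treatment comparison in general.* It does not if the gain is common to both arms. The effect sizes in Statistical Analysis are likewise contrasts between the groups, so a shared gain drops out of them too.
- *Practice differs by arm because control patients are unsupervised.* The statement "These activities will not require direct supervision" refers to the exercise and cognitive activities, not to the test visits. The documents give no attendance figures. On the assumptions in step 5, a gap of one or two visits would move the false-positive rate very little.
- *Each screen is given nine times.* That is one reading of a single section, and two others contradict it.

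It is also fair to say that alternate test forms are a detail an article may leave to the full protocol, and that removing interim visits would be a trade-off. Neither is claimed here as a defect. Cutting the number of tests would not validate the paired test either, since a single retest can produce a gain and other changes over time remain.

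**Conclusion.** The point holds for inference within an arm. With an assumed pure retest gain of 0.3 to 0.5 SD of change and no treatment effect, the planned paired test would be significant in about 31% to 69% of arms of 26, or 36% to 75% of arms of 30, against a nominal 5%. The size of the gain is an assumption and the percentages move with it. That a paired test cannot attribute change to treatment does not depend on the assumption, or on whether there are 2 or 9 assessments.

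The between-arm test keeps its 5% level under a gain common to both arms, and the documents do not show that attendance at assessments differs by arm. Separately, the sections conflict on when the outcomes are measured, so the visit on which the main comparison rests is not fixed.

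**What to change.** 1. In the abstract's Methods, the Objectives and Statistical Analysis, state that every efficacy conclusion, including those for cognition and for quality of life, rests on the randomised comparison between arms at one named post-intervention visit.
2. State in the same places that within-arm change is descriptive only.
3. Reconcile Selection of Participants with Trial Design and Participant Timeline on when the MMSE and the Montreal Cognitive Assessment are given, with the same schedule in both arms.

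The cost is a change of wording, with no effect on the sample size. The downside is that the paired tests can no longer be reported as evidence of effect. Within-arm means and changes can still be shown.

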### Participant Timeline

Pre- and postbaseline data will be collected, followed by a 4-week intervention period. After the completion of the 4 weeks, postintervention outcomes will be assessed. The study design is illustrated in the CONSORT flowchart presented in Figure 1.

### Control Group

Participants will perform aerobic exercises and cognitive behavioral training daily. The program will include brisk walking, cycling, jogging, and cognitive skill activities for 45 minutes per day, 5 days a week, over 4 weeks. These activities will not require direct supervision.

### Intervention Group

Domain-specific cognitive exercises to be administered to patients are outlined in Table 2.

**Table 2 table2:** Intervention group.

Problem identified		Physiotherapy intervention	Dosage		
